### Data collection and management

2.7

The whole process of data collection and recording will be recorded by 1 or 2 assistants. Personal information about potential participants and registered participants will be collected, shared and stored in a separate storeroom to protect confidentiality before, during and after the trial. Only the researchers of this research group have access to the relevant data of the study.

### Statistical analysis

2.8

The data will be analyzed by SPSS 16.0 software. The data of continuous variables of normal distribution will be tested by independent design *t* test, the data of continuous variables of skewed distribution will be tested by Mann–Whitney *U* test, and the data of classified variables will be tested by Chi-Squared test, and the difference is statistically significant when *P* *<* *.05.*

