### Distribution scheme

2.4

We plan to include 120 patients who meet the requirements, which are randomly divided into the observation group and the control group according to the ratio of 1:1. Random numbers will be generated by computer software programs designed by statisticians who are not familiar with the content of the study. The random numbers assigned to each group will be written on a piece of paper and placed in a sealed and opaque envelope. Envelopes will be provided to participants in random order. The evaluators in the trial do not know the random assignment of the participants. The statistics and analysis of the data will be completed by statistical researchers who have no knowledge of the grouping.

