### Observation index

2.6

1.The primary outcomes are duration of hospitalization, and clinical improvement 7 days after admission.2.The secondary outcomes are changing laboratory tests (IgA, IgG, and IgM) during 7 days, lung function, changing of CT findings after 30 days.3.Adverse reactions include gastrointestinal reactions, rash, dizziness, abnormal liver and kidney function, etc.

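### Section 2.8 sends all classified variables to the chi-squared test; if clinical improvement or CT change is recorded in three or more ordered grades, that test ignores the order

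*Protocol article*

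**What the plan says.** Section 2.8 (Statistical analysis) assigns tests by type of variable. Normally distributed continuous variables go to the t test. For skewed ones, "the data of continuous variables of skewed distribution will be tested by Mann–Whitney" U. For everything categorical, "the data of classified variables will be tested by Chi-Squared test". Ordered categories have no separate rule. The significance threshold is P < .05, and it is tied only to a difference: "the difference is statistically significant when" P falls below that value.

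Section 2.6 (Observation index) states: "The primary outcomes are duration of hospitalization, and clinical improvement 7 days after admission". Among the secondary outcomes it lists "changing of CT findings after 30 days". For neither improvement nor CT change does it say whether the record is yes/no, a set of grades or a numeric score.

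Section 2.4 (Distribution scheme) fixes the size: "We plan to include 120 patients who meet the requirements", "randomly divided into the observation group and the control group according to the ratio of 1:1". That is 60 per arm. The article gives no power, effect size or expected category rates.

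**The concern.** Clinical improvement and change on CT are both outcomes that are easily recorded in ordered grades, for example better, unchanged or worse. If they are, section 2.8 as written leads to a Pearson chi-squared test on a 2 × k table. That test treats the grades as unordered labels and spreads the comparison over k − 1 degrees of freedom.

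Two things follow:

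- **Power.** A consistent shift towards better grades is harder to detect than with a one-degree-of-freedom test that uses the order. The Discussion itself acknowledges that the sample is small.
- **Interpretation.** The test responds to any difference in pattern, including more children at both extremes. A P value below .05 then does not by itself answer whether the observation group did better.

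One of the two outcomes is primary, so a main conclusion of the trial could be affected.

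**Working it through.** The article states no power or effect size, so there is no figure of its own to reproduce. The check compares the stated test with an order-using one at the planned size.

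**Inputs from the document.** 120 children at 1:1 (section 2.4), so 60 per arm. Significance at P < .05 (section 2.8); sidedness is not given, so two-sided is assumed.

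**Assumed inputs.** Number of grades, grade distributions, a proportional-odds shift and no dropout. None of these is in the document.

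**1. Power by simulation** (20,000 trials per row). Pearson chi-squared with k − 1 degrees of freedom against tie-corrected Mann-Whitney:

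| Control grades, best to worst | Common odds ratio | Chi-squared | Mann-Whitney | Loss (points) |
|---|---|---|---|---|
| 50/35/15% | 2 | 37% | 47% | 10 |
| 50/35/15% | 2.5 | 60% | 69% | 9 |
| 25/35/25/15% | 2 | 37% | 54% | 17 |
| 25/35/25/15% | 2.5 | 61% | 78% | 17 |

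Repeat runs agree within about one point. With identical arms, both tests reject in about 5% of trials.

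**2. Sensitivity to the assumed distribution.** With evenly spread control grades and odds ratios from 2 to 3, the loss is about 7 to 10 points for three grades, 12 to 16 for four and 16 to 21 for five.

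**3. Yes/no case.** With 70% improved in the control arm and odds ratios of 2, 2.5 and 3, power is 37%, 53% and 67% with chi-squared and 35%, 51% and 65% with Mann-Whitney. The two tests are practically the same, and nothing is lost by using chi-squared.

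**4. Analytic check.** The noncentrality needed for 80% power at the 5% level is 7.85 on 1 df, 9.63 on 2 df and 10.90 on 3 df. If the whole effect lies along the ordered direction, the relative efficiency of chi-squared is:

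- three grades: 7.85 / 9.63 = 0.815, equivalent to losing about 120 × 0.185 ≈ 22 children;
- four grades: 7.85 / 10.90 = 0.72, equivalent to losing about 120 × 0.28 ≈ 34 children.

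Put the other way, an effect with 80% power on 1 df has 71% on 2 df and 64% on 3 df.

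**5. Significance without a direction.** Take observed counts of 20/10/10/20 in one arm and 10/20/20/10 in the other.

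- Every column total is 30, so every expected count is 15. Chi-squared = 8 × 5² / 15 = 13.33 on 3 df, P = 0.004.
- The midranks of the four grades are 15.5, 45.5, 75.5 and 105.5. The mean rank is (20 × 15.5 + 10 × 45.5 + 10 × 75.5 + 20 × 105.5) / 60 = 60.5 in the first arm, and (10 × 15.5 + 20 × 45.5 + 20 × 75.5 + 10 × 105.5) / 60 = 60.5 in the second. Mann-Whitney P = 1.00.

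In simulation, true distributions of 35/15/15/35% against 25/25/25/25% give rejection in 44% of trials with chi-squared and 5% with Mann-Whitney.

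**The case against.** The strongest reply is that the premise is not in the document. Section 2.6 never says that improvement or CT change is graded. Improvement may be yes/no, which suits chi-squared. CT change may be a numeric score, which section 2.8 would send to the t test or Mann-Whitney. The article is also condensed, and a fuller protocol or analysis plan may define the scales. This stands, and it is why the point is conditional. A reader might infer that the trial will certainly lose substantial power on these two outcomes; the document does not support that.

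Second, a reader might infer from the table in step 5 that chi-squared would produce false positives. It would not. The simulated arms there truly differ in spread, the test correctly rejects equality, and its level is about 5% when the arms are the same. The example is constructed, and nothing in the article suggests so polarised an effect. What remains is narrower: rejection would not show which arm did better.

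Third, the rank test has its own blind spot. A treatment that moved children to both extremes could increase the number with the worst grade, and Mann-Whitney would mostly miss it. That is a fair trade-off, and the fix has to cover it.

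Fourth, proportional-odds shifts favour the rank test, so the losses shown are for the setting in which it does well. This also stands as a limit on the figures.

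What the objections do not remove is the rule itself. Section 2.8 does more than stay silent on ordered data: it names one test for all classified variables and keeps the rank test for continuous ones. Read as written, an outcome in three or more ordered grades gets the unordered test.

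**Conclusion.** The point holds in conditional form. If either outcome has three or more ordered grades, the stated chi-squared test ignores the order. At 60 per arm and odds ratios of 2 to 2.5, the cost is about 10 points of power with three grades and about 17 with four, and a significant result need not mean that the observation group did better. The figures rest on assumed grade distributions, a proportional-odds shift and no dropout. For a yes/no outcome the cost is nil. Chi-squared remains a valid test at its 5% level in every case, so this is a matter of efficiency and interpretability and not of type I error. The other primary outcome, duration of hospitalization, is not affected. The change is worth making because it is right whichever scale is used.

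**What to change.** Before any outcome data are seen:

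1. In section 2.6, state the scale of clinical improvement at day 7 and of CT change at day 30: yes/no, ordered grades (with each grade defined) or numeric score.
2. In section 2.8, add a sentence to this effect: *Outcomes in three or more ordered grades will be compared between arms with the tie-corrected Mann-Whitney U test and reported with a proportional-odds common odds ratio and 95% confidence interval; the chi-squared test will be used for two-level or unordered variables.*
3. Tabulate the full grade distribution by arm for each such outcome, so that a shift to both extremes is visible even if the rank test does not detect it.

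The cost is a few lines of text. Mann-Whitney is already in the plan, no new data are needed, and yes/no outcomes are analysed as before. The one statistical price is lower sensitivity to a purely non-monotone difference, which the tabulation in item 3 is there to show.

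### Two unordered primary outcomes share one unadjusted P < .05 threshold; if either suffices for an efficacy claim, the type I error is up to 9.75%

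*Protocol article*

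**What the plan says.** Section 2.6 of the protocol article (Observation index) reads: "The primary outcomes are duration of hospitalization, and clinical improvement 7 days after admission". The two stand side by side. Neither is ranked above the other, and nothing says whether an efficacy claim needs one or both.

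Section 2.8 (Statistical analysis) assigns tests by type of variable:

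- Normally distributed continuous data: "The data of continuous variables of normal distribution will be tested by independent design" t test.
- Skewed continuous data: "the data of continuous variables of skewed distribution will be tested by Mann–Whitney" U test.
- Categorical data: "the data of classified variables will be tested by Chi-Squared test".

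It then sets one criterion for all of them: "the difference is statistically significant when" P < .05. The section does not separate primary from secondary outcomes, and it does not state sidedness.

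The sample size is in section 2.4 (Distribution scheme): "We plan to include 120 patients who meet the requirements", allocated 1:1, so 60 per arm. No effect size, power or family-wise error rate is given anywhere in the article.

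**The concern.** A trial with two primary outcomes has two chances of a false positive primary result, unless a rule links the tests. Here the only stated rule is a per-test threshold. Someone applying section 2.8 literally could call either primary outcome significant at .05 and report the combination as effective, whatever the other outcome showed. The 5% threshold would then no longer be the error rate of the primary claim.

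The open success rule is as important as the arithmetic. While the plan does not say whether one or both outcomes are needed, that choice can be made after the results are known. The Discussion says the trial is meant to supply a clinical basis for promoting the combined regimen, so the error rate behind that conclusion should be fixed in advance.

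**Working it through.** **Plan's own figure.** The article contains no derived error rate to reproduce. The .05 is a chosen threshold, and the 120 patients come without stated inputs.

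**Inputs from the article**

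- Number of primary outcomes: 2 (section 2.6).
- Threshold per test: α = 0.05, unsplit (section 2.8).
- Patients: 120 at 1:1, so 60 per arm (section 2.4). This is used only for the power cost.

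**Assumptions, because the article is silent**

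- Tests are two-sided, with critical value 1.96.
- Success means that at least one primary outcome is significant. The alternative, both significant, is shown as well.
- The correlation ρ between the two test statistics is varied from 0 to 1.

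**Step 1. Either outcome suffices, independent tests.**

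Family-wise error = 1 − (1 − 0.05)² = 1 − 0.9025 = 0.0975.

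Under any form of dependence it cannot exceed 0.05 + 0.05 = 0.10.

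**Step 2. Either outcome suffices, correlated tests.**

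Family-wise error = 1 − P(|Z₁| < 1.96 and |Z₂| < 1.96), with Z₁ and Z₂ bivariate standard normal with correlation ρ:

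| ρ | Family-wise error |
|---|---|
| 0 | 9.75% |
| 0.3 | 9.51% |
| 0.5 | 9.07% |
| 0.7 | 8.35% |
| 0.8 | 7.81% |
| 0.9 | 7.04% |
| 1 | 5.00% |

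Under this model independence gives the maximum, and the error stays above 5% for every correlation short of 1. Counting only false positives that favour Tanreqing, the figure under independence is 1 − (0.975)² = 4.94%, against 2.5% for a single primary outcome.

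**Step 3. Both outcomes required.**

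With no effect on either outcome and independent tests, the error is 0.05 × 0.05 = 0.0025. It can never exceed 0.05, because the outcome without an effect must still pass its own 0.05 test. No adjustment is needed.

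**Step 4. After adjustment.**

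With 0.025 per outcome, family-wise error = 1 − (0.975)² = 0.0494 under independence, and at most 0.025 + 0.025 = 0.05 under any dependence. Holm has the same 0.05 ceiling and rejects at least as often.

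**Step 5. Power cost.**

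Two-sample t test, 60 per arm, assumed standardised effect 0.5, noncentrality 0.5 × √(60/2) = 2.74, 118 degrees of freedom:

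- α = 0.05: power 77.5%.
- α = 0.025: power 68.0%.

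The 0.5 SD is an illustration and does not come from the article. It applies to a continuous outcome such as length of stay, and does not carry over to improvement at day 7 if that is analysed as a category.

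**The case against.** There are three serious objections.

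**The success rule is not in the text.** Section 2.8 says when a difference is significant, which is a per-comparison convention. Section 2.6 joins the two outcomes with a plain conjunction, and no sentence says that one positive result establishes efficacy. A reader might infer that the false positive rate simply is nearly 10%. The article does not support that: the figure needs both the either-suffices rule and independence. Children who improve sooner plausibly go home sooner, so some positive correlation is likely and the independence value is the top of the range. This objection stands, and the point is conditional for that reason.

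**Multiplicity rules often sit in the analysis plan, which is not shown.** This is right in part. A fixed order or a both-must-succeed rule would be compatible with P < .05 per test and could be added later without contradiction. A split or Holm, however, would have to change the threshold that section 2.8 states. The article is not silent on significance: it sets an unadjusted criterion and applies it to every test. The point therefore survives as a rule badly fixed, at reduced weight.

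**The secondary outcomes should not be pooled in.** A reader might also multiply the primaries by the immunoglobulins, lung function and CT, and quote a much larger chance of some significant result. That would treat related measures on the same children as independent, and would count outcomes that section 2.6 labels secondary as if they carried the primary claim. Nothing in the article says that they do, so no such figure is used here.

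The Discussion also concedes that the study is small and single-centre and needs confirmation in larger trials. That is a further reason not to overstate the matter.

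**Conclusion.** The point holds in conditional form. The article fixes two primary outcomes and one unadjusted threshold, and leaves open how the two results combine into a conclusion. If either suffices, the type I error of the primary claim is above the nominal 5%: at most 9.75% under the bivariate normal model, and roughly 9.5% to 7.8% for correlations of 0.3 to 0.8. That correlation range is assumed. If both must succeed, 0.05 per test is correct as it stands and only the statement of the rule is missing.

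The calculation is simple and secure. What is uncertain is which rule the investigators intend. This should be clarified and corrected before analysis; it is not a flaw that undermines the trial.

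**What to change.** Amend section 2.8 with one sentence, written before anyone sees outcome data by group, that adopts one of these:

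1. **Holm at a family-wise 0.05.** The smaller of the two primary P values is compared with 0.025 and, if it passes, the larger with 0.05. Either outcome may then support a claim. The power loss is at most that of a 0.025 split, about 78% to 68% in the illustration above, and less in practice.
2. **Fixed order, each at 0.05.** The first outcome loses no power. The second is tested only if the first succeeds, so its chance of being declared significant depends on the first. If improvement at day 7 is placed first, its definition and scale should be settled at the same time, since section 2.6 gives neither.
3. **Both must reach P < .05.** No adjustment is needed, but the joint requirement is harder to meet. With 77.5% power on each and independent tests, the chance of meeting both is 0.775² = 60%; positive correlation raises it.

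The same sentence should say that the tests are two-sided, if that is intended, and that the secondary outcomes are supportive. None of this affects the number of patients, the data collected or the treatment given.

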## Discussion

3

MP is an inflammation of alveoli, airways, or pulmonary interstitium caused by mycoplasma infection. It is a common pediatric disease,^[14,15]^ which can show a concentrated outbreak. The disease has the characteristics of urgent onset, rapid progress, critical condition, and easy recurrence, which seriously endangers the health of children.^[16]^

Azithromycin is a macrolide antimicrobial agent, and mycoplasma is more sensitive to it. But long-term intravenous injection may bring more adverse reactions, especially in children. Although sequential therapy can reduce adverse reactions, the possible drug resistance directly affects its efficacy.^[17]^ Tanreqing injection is a preparation of traditional Chinese medicine. Modern pharmacological studies have reported that Tanreqing injection can reduce the levels of tumor necrosis factor, interleukin (IL)-1, IL-6, and IL-8, inhibit the expression of inflammatory cytokines, improve airway mucus hypersecretion and airway inflammatory injury, and have anti-inflammatory, antibacterial and antiviral effects.^[18]^ The combination of the 2 drugs will improve the therapeutic effect, and studies have confirmed that the treatment scheme of integrated traditional Chinese and Western medicine is economical, safe, and effective.^[19]^ This study will evaluate the efficacy and safety of Tanreqing injection combined with azithromycin in the treatment of mycoplasma pneumonia in children through a strict randomized controlled scheme, so as to provide clinical basis for the promotion of this scheme.

As this study is a single center study, the small sample size and the regionalization of the included population may have a certain impact on the results, so more RCTs with more centers and large samples are needed to verify our conclusions.
